### Criteria for stopping the intervention

The intervention will be paused for significant hemodynamic changes, defined as a sustained (>15 min) increase or decrease in mean arterial pressure (MAP) of more than 30% from baseline or the last recorded stable value and is clinically symptomatic. It will be stopped if spinal cord perfusion pressure (SCPP) decreases to <65 mmHg for more than 15 min despite standard clinical management, including appropriate vasopressor titration. The intervention will also be paused for severe hemodynamic instability, such as persistent bradycardia, hypotension, or hypertension despite appropriate medical management, or for signs of autonomic dysreflexia, including sudden severe headache, flushing and profuse sweating above the level of injury, hypertension, bradycardia, anxiety, blurred vision, or nausea. Any serious adverse event deemed related to the intervention by the Principal Investigator or the safety monitor, or any unanticipated adverse device effect, will result in immediate suspension of the intervention pending further evaluation. If the patient experiences clinical deterioration that precludes participation (e.g., severe sepsis or coma), the intervention will be paused and reassessed. If the intervention is permanently discontinued, observational data collection will continue without further stimulation or sham trials until hospital discharge.

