We will measure glial fibrillary acidic protein (GFAP) and ubiquitin C-terminal hydrolase L1 (UCH-L1) in blood and CSF on the first day of stimulation prior to the first stimulation session (~72 h after injury). We will also measure these in blood on the final day of stimulation (treatment #5) or discharge, after last treatment, whichever is earlier. We will measure these in CSF on the final treatment before discharge, or before the lumbar drain is taken out if this happens before discharge, after treatment. GFAP and UCH-L1 will be assayed at ZSFG on the Abbott Alinity I Immunoassay system. At those same 2 time points we will also conduct a global discovery proteomic assay on both plasma and CSF. We will use the commercially available high-throughput protein biomarker discovery platform based on Olink’s Proximity Extension Assay (PEA), which reliably measures >5,400 proteins using <1 mL of biofluid.

At 6-month follow-up visit, participants will be asked about any adverse experiences and ISCNSCI with EMG assessment will be performed. We will also administer a modified DN4 and SCI Pain Basic Data Set questionnaire to assess presence of neuropathic or any other pain, the Spinal Cord Independence Measure (SCIM) to assess functional independence and Neuro-QoL (Lower Extremity function (Mobility) Short Form and Positive Affect and Well Being Short Form) to assess quality of life. See Figure 1 for a timeline of all study assessments.

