### Retention

Participant retention will be supported through financial compensation for completion of inpatient and 6-month follow-up assessments, provision of transportation, and flexible scheduling including in-home visits when feasible. Participants who discontinue or deviate from the intervention will be encouraged to complete all outcome assessments. Outcome data collected will include neurological measures (ISNCSCI with electromyography), patient-reported outcomes (DN4, SCI Pain Data Set, Neuro-QoL, SCIM), and adverse events to allow continued evaluation of safety and clinical outcomes.

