### Analysis of patient-reported secondary outcome measures

At 6-month follow-up, patient-reported outcome measures will be: neuropathic pain as measured by the DN4, quality of life as measured by the NeuroQoL, and functional independence measured by the SCIM. For DN4 data, incidence (count data) and severity (ordinal) will be assessed by Chi square and independent samples *T* test, respectively. NeuroQoL and SCIM measures will also be analyzed using independent samples *T* test.

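### After permanent discontinuation, the stopping section carries data collection only to hospital discharge, while the retention section seeks all outcome assessments, some of them scheduled only at 6 months

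*Protocol article*

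**What the plan says.** Two sections of the protocol article speak to the same participants.

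- **Criteria for stopping the intervention:** once treatment has been stopped for good, "observational data collection will continue without further stimulation or sham trials until hospital discharge".
- **Retention:** "Participants who discontinue or deviate from the intervention will be encouraged to complete all outcome assessments". The data to be collected are neurological measures (ISNCSCI with EMG) and "patient-reported outcomes (DN4, SCI Pain Data Set, Neuro-QoL, SCIM), and adverse events to allow continued evaluation of safety and clinical outcomes". The same section offers "financial compensation for completion of inpatient and 6-month follow-up assessments".

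The timing of those assessments is given elsewhere. Under Data collection methods: "At 6-month follow-up visit, participants will be asked about any adverse experiences and ISCNSCI with EMG assessment will be performed", with the modified DN4, the SCI pain data set, SCIM and Neuro-QoL given at that visit too. The section on patient-reported secondary outcomes agrees: "At 6-month follow-up, patient-reported outcome measures will be: neuropathic pain as measured by the DN4, quality of life as measured by the NeuroQoL", followed by SCIM. Table 1 also places DN4, Neuro-QoL and SCIM at 6 months. The legend to Figure 1 provides 6-month follow-up for both phases and makes no exception for participants who stop treatment.

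**The concern.** Staff who have just stopped a participant's treatment would look first at the section on stopping, and that section names the earlier end point. If they act on it, no 6-month visit takes place for that participant.

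The loss would not be random. Permanent discontinuation follows events such as low spinal cord perfusion pressure, a related serious adverse event or clinical deterioration, so who goes missing may depend on how treatment was tolerated or on prognosis. Two things are then at stake:

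- **The 6-month comparison of active and sham.** It would rest on a selected subset. The Sample size section says efficacy results will be used to estimate variability and effect sizes for later trials, and those estimates would inherit the selection.
- **Late safety.** The Harms section accepts that stimulation in the acute phase could in theory impair neurological recovery. The 6-month ISNCSCI and adverse-event query are the only checks after discharge that the article describes, and they would be missing for participants in whom that question is most pressing.

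**Working it through.** The plan states no figure to reproduce. The check is a comparison of text, followed by a short calculation of scale.

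**1. End point of data collection after permanent discontinuation**

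| Section | End point |
|---|---|
| Criteria for stopping the intervention | Hospital discharge |
| Retention | All outcome assessments (encouraged), in a section that covers inpatient and 6-month assessments |

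**2. Does discharge come before the 6-month assessments?** Yes. The Introduction puts the initial hospitalization at 11 days on average.

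**3. Can the Retention list be completed by discharge?** No. Wherever SCIM and Neuro-QoL are given a time point (Table 1, Data collection methods, the patient-reported analysis section), it is 6 months. The Figure 1 legend mentions patient-reported measures at baseline and at 7 days without naming them, and Data collection methods lists only pain questionnaires at baseline. A participant followed only to discharge therefore cannot supply SCIM or Neuro-QoL.

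**4. What a literal reading of the stopping section loses:** DN4, SCIM and Neuro-QoL at 6 months; ISNCSCI with EMG at 6 months; the 6-month adverse-event query.

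**5. What it does not touch:** the primary outcomes in Table 1. Safety is counted as events over sessions, and the Phase 2 lower motor score is compared during tSCS and from baseline to after tSCS. Both are obtained in hospital.

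**6. Scale.** The Trial design section plans 5 active and 5 sham participants. One loss is 1/5 = 20% of an arm and two are 2/5 = 40%. The article gives no discontinuation rate, so 0 to 2 losses are assumed here to show a range. The 95% confidence interval half-width for a difference in means, in SD units, is t(0.975, n1+n2−2) × √(1/n1 + 1/n2):

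| Followed to 6 months | √(1/n1 + 1/n2) | Half-width (SD) | Relative to 5 v 5 |
|---|---|---|---|
| 5 v 5 | 0.6325 | 1.46 | – |
| 4 v 5 | 0.6708 | 1.59 | 1.586/1.458 = 1.09 |
| 4 v 4 | 0.7071 | 1.73 | 1.730/1.458 = 1.19 |
| 3 v 5 | 0.7303 | 1.79 | 1.787/1.458 = 1.23 |

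**7. Bias.** Suppose four participants in an arm have mean m and the missing fifth would have scored m + δ. The full arm mean is (4m + m + δ)/5 = m + δ/5, and the observed mean is m. The error is −δ/5 in that arm. Neither the size nor the sign of δ is given in the documents, nor which arm would lose the participant, so the direction of the effect on the comparison cannot be stated.

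**The case against.** The strongest reply is that the document already deals with this group. The Retention section addresses discontinuers directly, names the 6-month instruments and adverse events, and pays for the visit. The Figure 1 legend and Data collection methods plan the visit for everyone. The sentence in the stopping section can also be read as covering only the hospital stay: inpatient observation goes on without stimulation, and the 6-month visit follows as usual. It nowhere says that a participant leaves the study.

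Much of this stands. It shows which rule was probably intended, and it makes the problem one of wording rather than of design. It does not remove the conflict, because the inpatient-only reading is possible but unstated. Attaching the discharge limit to the stimulation instead adds little, since stimulation is given only in hospital.

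The reply also rightly limits who is affected. Most triggers in the stopping section pause or suspend the intervention, and the disputed sentence applies only once discontinuation is permanent. Sepsis or coma can lead to it in either arm, so these are not simply people who could not tolerate stimulation.

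Three stronger readings are tempting, and the documents do not support them:

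- **That the loss would favour active tSCS.** This needs the lost participant to be in the active arm and to do worse than the rest. The article supports neither assumption.
- **That late safety will go unobserved in discontinuers.** The Retention section lists adverse events for exactly these participants.
- **That discontinuers will be removed from their randomized arm in the analysis.** The article does not say so, and the analysis population is a matter for a statistical analysis plan that is not shown.

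**Conclusion.** The point holds as an unreconciled inconsistency about how long data are collected after permanent discontinuation. The outcomes exposed are the 6-month secondary outcomes, the 6-month ISNCSCI with EMG, and the late adverse-event query, in either arm.

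The consequence arises only if the stopping section is followed literally. In that case each permanently discontinued Phase 2 participant costs 20% of a planned arm, and the loss may be related to tolerability or prognosis. The interval widths under Working rest on assumed losses and serve only as scale. The Sample size section already calls the efficacy analyses exploratory, so the loss of precision matters less than the selection. Even with the clause repaired, Retention promises encouragement, so completion is sought and not guaranteed.

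The clause should be corrected. The finding does not call the primary outcomes or the design into question.

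**What to change.** In the section on criteria for stopping the intervention, replace the limit at hospital discharge with: *through the 6-month visit, on the planned assessment schedule, unless consent for follow-up is withdrawn*. This brings the sentence into line with the Retention section. If the investigators did mean collection to end at discharge, the Retention section would have to say so instead; either way the two must agree.

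The cost is one clause. The 6-month visit, transport, compensation and flexible scheduling are already planned. The change concerns data collection only and leaves the criteria for pausing or stopping the intervention as they are.

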### Concomitant and post-trial care

Participation in the study will not alter provision of standard of care during or post-trial. Individuals who consent to participate in the study, will however, have additional experimental assessment and treatment procedures incorporated while they are in ICU. The additional assessments will include blood draws and testing of motor evoked potentials using tSCS. The additional treatment will include a single 60 min of tSCS for Phase 1 participants and 5 days of once daily 60 min of active tSCS or sham tSCS. The frequency of certain standard of care procedures, such as ISNCSCI to assess the neurological status of the participant will be increased to daily assessments. The adherence to intervention protocol will be directly monitored by the research staff who will conduct all experiments during the in-patient hospital stay. Any adverse events related to study procedures will be managed promptly by the clinical team according to institutional standards. Compensation for research-related injury will be provided in accordance with University of California, San Francisco institutional policies. No additional post-trial interventions are planned.

### Outcomes

Table 1 lists all trial outcome measures and the corresponding abbreviated statistical analysis plan.

**Table 1 tab1:** A list of outcome measures and the corresponding analysis plan.

Outcome measure	Description	Statistical analysis
Primary outcomes (safety)—Phase 1 and 2		
1. Incidence of adverse events (# of observed events/sessions)	Hemodynamic instability Skin irritation Patient condition deterioration Unanticipated adverse events	Data type: Count Data Statistical Test: Fisher’s Exact Test
Primary outcomes (efficacy)—Phase 2		
1. ISNCSCI lower motor scores	Immediate change in scores with acute tSCS Change in scores from baseline to post tSCS	Data Type: Integer Statistical Test: Repeated Measures Analysis of Variance
Secondary outcomes (efficacy)—Phase 1 and 2		
1 ISNCSCI sensory + motor scores	Change in scores from baseline to 7DPI or discharge	Data Type: Integer Statistical Test: Repeated Measures Analysis of Variance
2. Spinally motor evoked potentials (MEPs)	MEP present/elicited (binary measure) (within subject) # of muscles with elicitable MEP	Data Type(s): Binary, Count Statistical Tests: Chi-Square, Fisher’s Exact Test
3. Electromyography (EMG) amplitude	Change in EMG amplitude in the presence of tSCS vs. no stimulation (within subject) Change in number of muscles with EMG output	Data Type(s): Continuous, Count Statistical Tests: Repeated Measures Analysis of Variance, Fisher’s Exact Test
Secondary outcomes (biomarker discovery)—Phase 1 and 2		
1. Neuronal (UCH-L1) and glial cell (GFAP) injury markers in blood	Changes in protein levels from baseline to post tSCS vs. sham	Data Type: Continuous Statistical Tests: Repeated Measures Analysis of Variance
2. CSF proteomics	Changes in protein levels from baseline to post tSCS vs. sham	Data Type: Continuous Statistical Tests: Non-linear Principal Components Analysis, followed by RM-ANOVA on PC scores
Secondary outcomes (patient-reported outcomes)—Phase 1 and 2		
3a. Incidence of neuropathic pain at 6-month follow-up 3b. Severity of neuropathic pain at 6-months follow-up	Modified DN4 questionnaire will be used to assess neuropathic pain at 6-months follow-up in tSCS vs. sham individuals (vs. historical TRACK-SCI participants)	Data Type: Integer, or Binarized at ≤ indicating neuropathic pain Statistical Test: Independent group Student’s *t*-test, or Chi-square
4. Quality of life	Neuro-QoL questionnaire will be used to assess patients’ quality of life at 6-months follow-up	Data Type: T score Statistical Test: Independent group Student’s *t*-test
5. Functional independence	Spinal Cord Independence Measure, Version 3 will be administered to assess functional independence at 6-months follow-up	Data Type: Integer (0–100) Statistical Test: Independent group Student’s *t*-test

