### Objectives

This study has three main objectives. First, test the safety of tSCS applied below the level of injury to the lumbosacral spinal cord after acute spinal cord injury, starting 72 h after injury. We hypothesize that there will be no adverse events associated with acute application of tSCS. Second, demonstrate the proof-of-principle that tSCS application in the acute phase post-injury can potentiate recovery. We hypothesize that tSCS can improve volitional movement and/or sensation acutely after SCI as measured by an improved lower extremity motor score in the presence of tSCS. Third, identify treatment-related mechanistic biomarkers (exploratory). We hypothesize that there will be fluid-based biomarkers that will change in the setting of tSCS receipt.

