### Trial design

We will conduct a Phase 1 and Phase 2 clinical trial (Figure 1). Phase 1 is an open label study focused on determining safety of the initial 60 min of tSCS between 72 and 96 h after spinal cord injury (*n* = 5). Phase 2 is a randomized, placebo-controlled triple-blinded clinical trial with a parallel group assignment (active tSCS, *n* = 5 and sham tSCS *n* = 5) focused on determining safety and efficacy of tSCS for treatment of acute SCI. A total of 15 subjects will be enrolled across Phase 1 and Phase 2. A sham-controlled design was selected to isolate the physiological effects of electrical stimulation from nonspecific influences related to device application, participant expectations, investigator interaction, and increased clinical monitoring.

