### Intervention and comparator

Transcutaneous spinal stimulation will be delivered using ARC^EX^ device (ONWARD Medical), via skin surface electrodes placed over the spine targeting lumbosacral spinal cord at T10 and L1 using round 3.2 cm in diameter stimulating electrodes, and bilaterally on the iliac crests using rectangular, 7.5 × 13 cm reference electrodes during the intervention. Based on previous studies on safety and efficacy of tSCS, we will use biphasic waveforms with a burst frequency of 30 Hz, a carrier frequency of 10 kHz, with a pulse width of 1,000 μs (Gerasimenko et al., 2015; Keller et al., 2021; Moritz et al., 2024). Stimulation will be delivered continuously for 60 min once (for Phase 1 participants) and once a day for 5 consecutive days (for Phase 2 participants). The intensity of the stimulation will be increased gradually to the motor threshold intensity (Moritz et al., 2024) and lowered until motor responses subside if there are any. Increase in trunk/lower extremity muscle tone will be additionally monitored to assess whether the amplitude of stimulation required to reach motor threshold changes with days post injury + tSCS treatment for Phase 2 participants. If stimulation does not elicit any obvious motor responses due to spinal shock, the stimulation intensity will be chosen based on previously reported ranges of effective stimulation, including those observed in our ongoing clinical trial in patients with chronic low back pain (NCT05265000) which provides ranges of maximum tolerable stimulation intensities in individuals without SCI, who have full sensation. The stimulation parameters used in that study are identical to those proposed in STEP-RAISE, including waveform, pulse width, carrier frequency, and electrode configuration, allowing for adaptation of stimulation intensities if necessary. The specific stimulation parameters and optimal stimulation intensity will be left to the discretion of the investigators during this experimental treatment. A range of the investigated stimulation parameters will be systematically recorded and will be reported as part of the methodology for each participant. The stimulation will be delivered while the participant is lying supine in the ICU bed. The lower motor ISNCSCI exam will be performed within the last 30 min of stimulation to assess whether acute tSCS potentiates volitional lower extremity movement. Although physical therapy (PT) is provided to acute SCI patients, in this trial the goal is to assess whether tSCS alone can be delivered safely, and will not be combined with the standard of care ICU PT. Participants will be continuously monitored and asked to provide any verbal feedback regarding stimulation to ensure there is no pain or discomfort during treatment.

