### Analysis of primary and secondary efficacy outcome measures

For all participants, the primary outcome measure(s) will be: incidence of adverse events (number) for Phase 1 and 2 and change in ISNCSCI lower motor score over time for Phase 2. Secondary outcomes in both phases will be: ISNCSCI sensory scores, AIS grade, peak EMG amplitude, and mean EMG amplitude. For Phase I, change scores will be measured between baseline and post-trial, and in Phase II each measure will be taken across 5 trials. For all repeated measures analyses, we will use a factorial within-subjects repeated-measures analysis of variance (RM-ANOVA) to assess statistically significant change over time. This approach will allow us within a single statistical test to assess (1) the overall between-subjects effect of stimulation to determine the group differences between the stimulation and control groups, (2) the difference in changes over time between groups, and (3) the within-subjects effect of stimulation over trials, to determine the extent to which each individual changes over time. The RM-ANOVA procedure will be run for each outcome measure.

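### The only denominator given for the primary safety outcome is sessions, so Fisher's exact test in Phase 2, followed as written, treats five sessions of one person as five independent units

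*Protocol article*

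**What the plan says.** In the protocol article, Table 1 (Outcomes) has one safety row, headed "Primary outcomes (safety)—Phase 1 and 2". The outcome is "Incidence of adverse events (# of observed events/sessions"), covering hemodynamic instability, skin irritation, deterioration of the patient's condition and unanticipated events. The analysis entry is "Data type: Count Data Statistical Test: Fisher’s Exact Test".

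The section on analysis of primary and secondary efficacy outcome measures restates the outcome as "incidence of adverse events (number) for Phase 1 and 2". It gives no participant-level definition and no method for repeated sessions.

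Under Intervention and comparator, stimulation is given "once (for Phase 1 participants) and once a day for 5 consecutive days (for Phase 2 participants"). Trial design plans five active and five sham participants in Phase 2. It describes the other phase thus: "Phase 1 is an open label study focused on determining safety of the initial 60 min of tSCS", with five participants and no control group. The data management and interim analysis sections give Phase 1 a qualitative safety review before Phase 2 starts.

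The safety hypothesis under Objectives is: "We hypothesize that there will be no adverse events associated with acute application of tSCS". No acceptable event rate or margin is stated.

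**The concern.** Fisher's exact test compares two proportions made up of independent yes/no units. Sessions of one participant need not be independent: a person whose skin reacts under the electrode on day 1 may well react on days 2 to 5. If sessions are the units, one or two susceptible people can supply most of the events in an arm, and the test reads that as evidence about 25 units.

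There is also a problem of fit. One session can produce more than one listed event, for example a skin reaction and a blood pressure change. Events over sessions is then not a proportion, can exceed 1, and does not form a 2x2 table.

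Safety is the first objective, and the statement that the trial is exploratory (Sample size section) covers efficacy only. At stake is whether the Phase 2 safety comparison of active with sham gives a p-value that means what it appears to mean.

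**Working it through.** **Plan's own figure.** None. The article gives no power, margin or acceptable rate for safety, so there is nothing to reproduce. Alpha 0.05 appears only in the Sample size section; two-sided testing is assumed here.

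**Design counts.** Phase 1: 5 participants × 1 session = 5 sessions. Phase 2: 5 × 5 = 25 active and 5 × 5 = 25 sham sessions, if the planned 5:5 split is achieved.

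**Illustration, two-sided Fisher.** With all events in one arm and equal arms of size m, p = 2·C(m,k)/C(2m,k).

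| Active participants affected (none in sham) | By session | By participant |
|---|---|---|
| Two, at all five sessions each | 10/25 v 0/25: 2·C(25,10)/C(50,10) = 0.0006 | 2/5 v 0/5: 2·C(5,2)/C(10,2) = 20/45 = 0.44 |
| Two, six event sessions between them | 6/25 v 0/25: 2·C(25,6)/C(50,6) = 0.022 | 2/5 v 0/5: 0.44 |
| One, at all five sessions | 5/25 v 0/25: 0.0502 | 1/5 v 0/5: 1.00 |

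**Type I error of the session-level test.** Inputs assumed, because the documents give none: an event rate per session of 10%, 20% or 30%, equal in both arms, and a within-person correlation ρ. Each session is scored yes or no. A participant's number of event sessions out of five is beta-binomial with parameters p(1−ρ)/ρ and (1−p)(1−ρ)/ρ, or binomial at ρ = 0. The two arm totals were enumerated in full and the probability of all tables with Fisher p ≤ 0.05 was summed.

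| ρ | rate 10% | rate 20% | rate 30% | design effect 1+4ρ |
|---|---|---|---|---|
| 0 | 0.9% | 2.2% | 2.3% | 1.0 |
| 0.1 | 2.7% | 5.2% | 5.7% | 1.4 |
| 0.3 | 7.2% | 12.3% | 13.7% | 2.2 |
| 0.5 | 11.4% | 19.1% | 21.2% | 3.0 |
| 0.7 | 13.8% | 24.2% | 27.5% | 3.8 |

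The test is conservative when sessions are independent, about nominal at ρ = 0.1, and above 5% at every rate tried from ρ = 0.3.

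**Participant as unit, 5 v 5.** The splits that reach p<0.05 are 4–0 (0.048), 5–1 (0.048), 5–0 (0.008) and their mirror images. 3–0 gives 0.17. With assumed true proportions affected of 60% v 10%, power is 22%.

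**What zero events would exclude.** The two-sided 95% Clopper-Pearson upper limit for 0/n is 1 − 0.025^(1/n). For n = 5 this is 52%; it applies separately to the five-session active arm and to the single-session Phase 1 group. For n = 10, pooling all active participants, it is 31%, but that pool mixes one-session with five-session exposure.

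**The case against.** The strongest defence is that the article never says that sessions are the units entered in the test. It introduces Table 1 as an abbreviated plan, the analysis section gives only a number of events, and the parenthesis could be a reporting rate, with Fisher's test applied to participants. A full analysis plan might say so. This stands to the extent that session-level testing is what follows from the text, not something it announces. It does not remove the point: events over sessions is the only denominator given, and a participant-level plan would have to replace it.

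Second, the inflation depends on assumed inputs. This stands: at correlations of 0 to 0.1 the error is about 1-6%. The p=0.0006 illustration is also an extreme case, needing events at all ten sessions of two people and none elsewhere. The stopping rules could limit repetition of the more serious events.

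Third, a reader might infer that Phase 1 safety depends on a test that cannot be run with one arm. The documents do not support this. Phase 1 gets a qualitative review before Phase 2, and the table row simply covers both phases. The label needs correcting; the Phase 1 decision is not affected.

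Fourth, a reader might infer that a non-significant result will be taken as proof of the no-events hypothesis. Nothing in the article says so. Events are graded individually for severity and relatedness, and a single event judged related would contradict the hypothesis without any test.

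Finally, a per-session rate ties events to exposure, and any-cause events may be common in both arms among ICU patients. Both are reasons to keep the rate as description and to count device-related events separately.

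**Conclusion.** The point holds for Phase 2. The stated denominator does not suit the stated test: as written, 50 sessions from ten people enter a test that needs independent binary units, and a session with several events does not fit the test at all. The same data can give p=0.0006 by session and 0.44 by participant. The type I error is 7-27% for assumed session rates of 10-30% and within-person correlations of 0.3-0.7, but only 1-6% for correlations of 0-0.1. These figures assume at most one counted event per session, a beta-binomial model, equal rates in the two arms and the planned 5:5 split. The rates and correlations are assumptions throughout.

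Pausing and stopping, the review of individual harms, and the move from Phase 1 to Phase 2 do not use this p-value. What is affected is the reported Phase 2 comparison on a primary outcome.

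**What to change.** 1. For Phase 2, define the primary safety outcome by participant: the number and proportion with at least one adverse event and, separately, with at least one device-related event. Report each by arm with an exact 95% interval, and give an exact interval for the difference between arms.
2. Keep events per session as a descriptive exposure rate, without Fisher's test.
3. Label Fisher's test in Table 1 as Phase 2 only. Report Phase 1 descriptively with an exact interval, in line with the qualitative review already planned.
4. State beside the no-events hypothesis what zero events would exclude, by regimen: 0/5 leaves an upper limit of 52% for the five-session active arm, and likewise for the single-session Phase 1 group. Quote the pooled 0/10 limit of 31% only with the caveat that exposure differs.

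The cost is rewording Table 1 and the objective. No new data are needed, and the blind is to be kept until database lock, so the change can be made before unblinding. The drawback is low power: at 5 v 5 only near-complete separation reaches p<0.05, so the intervals must carry the result and the safety statement becomes less favourable.
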